### Economic evaluation

We plan an economic evaluation alongside the clinical trial to investigate the cost-effectiveness of the multifaceted implementation strategy to improve guideline adherence on TEM. This economic evaluation compares the multifaceted implementation strategy to usual care and is done from a societal perspective. A distinction will be made between costs of the development and introduction of the implementation strategy and the costs of maintaining the implementation strategy. The input of resources is assessed by collecting volumes of consumed resources (*e.g.*, medical interventions like number IUI and IVF cycles and treatment related outcomes like ovarian hyperstimulation syndrome and multiple pregnancies) and multiplied by reported or guideline prices according to Oostenbrink [29]. To assess non-medical and indirect costs, we will build on the data collection and cost calculation frameworks from previous cost studies on IUI and IVF [30,31]. The incremental costs, expressed as costs/percentage guideline adherence to TEM, are determined by the differences in resource consumption and adherence rates between the intervention group and the control group. Robustness of the results (costs and health outcomes) for various assumptions and parameters estimates will be explored in sensitivity analyses and visualized in incremental cost-effectiveness ratio graphs and cost-effectiveness acceptability curves.

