### Secondary outcomes effectiveness

1. Treatment-related measures: time to the start of fertility treatment and the number and types of fertility treatments that the couples received.

2. Treatment outcome-related measures: (ongoing) pregnancy rate, miscarriage, extra uterine gravidity, multiple pregnancy rate, and time to pregnancy.

3. Patient-related outcome measures : general experiences with fertility care such as information provision, respect for patients’ values and accessibility of care (to be measured with Patient Centeredness Questionnaire Infertility) [26], specific experiences with the prognostic model and TEM, quality of life (estimated by FertiQoL)[27], and trust in physician (measured by Wake Forest Trust Scale) [28].

4. Process related measures: percentage transition of patients to another fertility center.

5. Background characteristics that could influence guideline adherence (*e.g.*, age, referral status, type of infertility, duration and cause of infertility).

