## Discussion

This cluster RCT will compare a multifaceted implementation strategy to usual care on improving guideline adherence to TEM. If TEM is applied more frequently, it will reduce the number of performed IUI, IVF, and ICSI cycles, the incidence of treatment related complications (*e.g.*, ovarian hyperstimulation syndrome and multiple pregnancies), and we expect it to reduce the physical and psychological burden. As a consequence, the costs for fertility treatment will decrease.

Many different interventions are available to implement guidelines, either focusing on professionals, patients, teams or organizational factors, and with variable effects. A systematic review on interventions to improve guideline implementation showed that interventions tailored to prospectively identified barriers are more likely to improve professionals practice than only dissemination of guidelines [32]. The strategy that we developed is tailored to the recently identified barriers and facilitators for TEM, thus more likely to improve professionals practice, in this case, adherence to the guideline. Moreover, in general, combined interventions are believed to be more effective than single interventions [32]. Therefore, to increase the potential effectiveness of our implementation strategy, we developed a multifaceted intervention that targets the specific barriers for TEM at different levels.

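### The economic evaluation names only adherence, a process measure, as its effect, so a pregnancy difference between arms gets no weight in the cost-effectiveness result

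*Protocol article*

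**What the plan says.** All places are in the protocol article.

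- **Economic evaluation, perspective:** "This economic evaluation compares the multifaceted implementation strategy to usual care and is done from a societal perspective".
- **Economic evaluation, effect unit:** "The incremental costs, expressed as costs/percentage guideline adherence to TEM, are determined by the differences in resource consumption and adherence rates". No other effect unit is named.
- **Economic evaluation, costs:** the resources, given as examples, are "medical interventions like number IUI and IVF cycles and treatment related outcomes like ovarian hyperstimulation syndrome and multiple pregnancies". The section also separates "costs of the development and introduction of the implementation strategy and the costs of maintaining the implementation strategy", and plans to count non-medical and indirect costs.
- **Economic evaluation, uncertainty:** "Robustness of the results (costs and health outcomes) for various assumptions and parameters estimates will be explored in sensitivity analyses", with results "visualized in incremental cost-effectiveness ratio graphs and cost-effectiveness acceptability curves".
- **Primary outcome effectiveness:** adherence is the percentage of eligible couples who agree to an expectant period of six months or more.
- **Secondary outcomes effectiveness:** "Treatment outcome-related measures: (ongoing) pregnancy rate, miscarriage, extra uterine gravidity, multiple pregnancy rate, and time to pregnancy". These are not linked to the economic evaluation.
- **Background:** with a prognosis of 30% or more, expectant management for 6 to 12 months is taken to be as effective as treatment.
- **Discussion:** after predicting fewer treatment cycles and complications, "As a consequence, the costs for fertility treatment will decrease".

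**The concern.** The strategy moves couples from treatment to waiting. The outcome that could suffer is pregnancy, and an evaluation with a societal perspective would be expected to show it. The only effect in the stated result is agreement to a policy. The sentence on sensitivity analyses refers to health outcomes, but the section defines none: ovarian hyperstimulation syndrome and multiple pregnancy appear only as items to be costed.

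The economic conclusion therefore takes the equal-effectiveness premise as given. If that premise failed in these clinics, the cost-effectiveness result would look the same on its effect side.

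A second, smaller matter is the form of the result. If net cost falls and adherence rises, a cost-per-point ratio is negative, and its size does not say which result is better.

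**Working it through.** **1. The figures the protocol gives.** It states no economic figure. The nearest computed one is the sample size, which supplies the adherence difference used below. Inputs (Sample size section): 60% v 80%, ICC 0.1, alpha 5%, 25 clinics. Assumed: two-sided test, 80% power.

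- Per arm without clustering: [1.96·√(2·0.7·0.3) + 0.842·√(0.6·0.4 + 0.8·0.2)]² / 0.2² = 81.2, so 82.
- Couples per clinic: 450/25 = 18. Design effect: 1 + 17·0.1 = 2.7.
- Total: 2·82·2.7 = 442.8, or 24.6 clinics of 18, rounded up to 25·18 = 450.

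The stated 450 is reproduced. The planned effect is ΔE = +20 points, with about 225 couples per arm at the after measurement.

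**2. Weight given to pregnancy.** Let ΔC be incremental cost per couple, ΔE incremental adherence in points and ΔP the difference in ongoing pregnancy. The stated result is ΔC/ΔE, which does not contain ΔP. Assume ΔC = -1000 (arbitrary units), ΔE = +20, and that a pregnancy difference leaves cost unchanged:

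| ΔP (assumed) | Cost per adherence point | On a pregnancy scale |
|---|---|---|
| 0 | -1000/20 = -50 | saving, no pregnancies lost |
| -2 points | -50 | 1000/0.02 = 50,000 saved per pregnancy forgone |
| -5 points | -50 | 1000/0.05 = 20,000 saved per pregnancy forgone |

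The adherence result is the same in all three rows, although they pose different decisions.

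If each pregnancy instead carried an assumed cost of 2000 to 5000 in the numerator, losing 2 to 5 points would move ΔC to between -1000 - 0.02·2000 = -1040 and -1000 - 0.05·5000 = -1250. The ratio would become -52 to -62.5. Later treatment of couples who did not conceive would push ΔC the other way. The documents do not settle which effect is larger.

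**3. Ordering of the ratio.** Net benefit is λ·ΔE - ΔC, where λ is the assumed value of one adherence point.

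| ΔC | ΔE | ΔC/ΔE | Net benefit at λ = 0 / 50 / 100 |
|---|---|---|---|
| -1000 | +20 | -50 | 1000 / 2000 / 3000 |
| -1000 | +5 | -200 | 1000 / 1250 / 1500 |
| +1000 | -20 | -50 | -1000 / -2000 / -3000 |
| +1000 | +20 | +50 | -1000 / 0 / 1000 |

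Rows 1 and 3 share one ratio, although one is the best outcome and the other the worst. Row 2 has the more negative ratio but is never better than row 1. Net benefit separates rows 1 and 3 at every λ shown. Row 4 is the case where strategy costs exceed treatment savings, and there the ratio reads normally.

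**4. Precision of a pregnancy comparison.** With 225 couples per arm and an assumed pregnancy rate of 35%, the 95% half-width is 1.96·√(2·0.35·0.65/225) = 8.8 points with no clustering. Multiplied by √2.7 = 1.643 (ICC 0.1 borrowed from adherence), it is 14.5 points. Assumed rates of 30% to 40% give 8.5 to 9.1 and 13.9 to 14.9 points.

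**The case against.** Four arguments on the other side have force.

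- **The effect unit fits the question.** The aim is to evaluate a strategy for raising adherence. Given the Background premise, cost per unit of adherence is a coherent choice for an implementation trial. This stands as a reason to keep the adherence result, but not as a reason to leave pregnancy out: the premise is an assumption, and the trial collects data bearing on it.
- **The trade-off is not hidden from the trial as a whole.** Pregnancy outcomes are compared between arms, and time to pregnancy has its own Kaplan-Meier and log-rank analysis. This stands. The gap is confined to the economic conclusion, where costs and pregnancies are never brought together.
- **The planned displays help.** Ratio graphs drawn as a plane show the quadrant, and acceptability curves based on net benefit stay defined when costs fall. This largely answers the ordering problem, but both displays would still use adherence as the effect. The lack of a stated threshold is no defect, since such curves are drawn over a range of values and an article may leave that detail to the full plan.
- **A pregnancy-based result will be imprecise.** This also stands: a 5-point loss lies well inside a half-width of about 9 to 14 points.

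A reader might infer more than the text supports. One inference is that the protocol expects a negative ratio. The Discussion predicts lower fertility-treatment costs only, while the Economic evaluation section adds the costs of developing, introducing and maintaining the strategy, so the net sign is open. Another is that a lost pregnancy is booked as a pure saving. The resource list gives examples only and names multiple pregnancies, not singletons, and couples who do not conceive may generate later costs. What follows from the text is narrower: such a loss has no weight on the effect side.

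**Conclusion.** The point holds in a limited form. The Economic evaluation section fixes a single process measure as its effect and refers to health outcomes that it never defines. A pregnancy difference of any size leaves the effect side unchanged, so the cost-effectiveness conclusion depends on the equal-effectiveness premise without being able to reveal its failure. The ordering problem arises only if net cost falls while adherence rises, which the protocol neither states nor rules out, and the planned displays meet most of it.

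Every monetary value, λ and pregnancy rate above is an assumption; only the 20-point difference, the ICC and the 450 couples come from the protocol. No sample-size, power or alpha figure changes, and the primary effectiveness analysis is unaffected. Severity is minor: this is a cheap improvement.

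**What to change.** In the Economic evaluation section:

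1. Report incremental cost per couple and incremental adherence separately, with their joint uncertainty. Use net benefit in place of the bare ratio whenever the ratio would be negative.
2. Add ongoing pregnancy as a second effect measure over the same time horizon, with its own cost-effectiveness plane and net-benefit acceptability curve beside the adherence result. This would also give the reference to health outcomes a defined meaning.
3. Show the case of lower cost with fewer pregnancies on the plane and as savings per pregnancy forgone. A rule that allowed a ratio only when both differences are positive would suppress that case.

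The cost is some extra analysis of data already planned: pregnancy outcomes are abstracted from medical records. The Trial status section places the study at baseline measurement, so the change can precede any after-measurement data. The downside is an imprecise pregnancy-based result, which should be reported with its interval and not read as evidence of no difference.

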### Trial status

We are currently performing the baseline measurement in all participating clinics.

## Discussion

This cluster RCT will compare a multifaceted implementation strategy to usual care on improving guideline adherence to TEM. If TEM is applied more frequently, it will reduce the number of performed IUI, IVF, and ICSI cycles, the incidence of treatment related complications (*e.g.*, ovarian hyperstimulation syndrome and multiple pregnancies), and we expect it to reduce the physical and psychological burden. As a consequence, the costs for fertility treatment will decrease.

Many different interventions are available to implement guidelines, either focusing on professionals, patients, teams or organizational factors, and with variable effects. A systematic review on interventions to improve guideline implementation showed that interventions tailored to prospectively identified barriers are more likely to improve professionals practice than only dissemination of guidelines [32]. The strategy that we developed is tailored to the recently identified barriers and facilitators for TEM, thus more likely to improve professionals practice, in this case, adherence to the guideline. Moreover, in general, combined interventions are believed to be more effective than single interventions [32]. Therefore, to increase the potential effectiveness of our implementation strategy, we developed a multifaceted intervention that targets the specific barriers for TEM at different levels.

For the specific interventions that will be used in the multifaceted implementation strategy, the review showed that audit and feedback and educational outreach visits can be effective (small to moderate) [32-34] and patient-directed interventions such as educational materials may result in moderate to large effects to increase adherence to recommended care [32]. Moreover, it has been proven that subfertile patients appreciate education and improved knowledge, and it has also been demonstrated to influence their healthcare decisions [35,36]. In a systematic review, only the effect of paper version materials was studied. However, because surveys have shown that online health information retrieval and eHealth activities are becoming increasingly common, especially within young and highly educated subfertile patients [37-40], we decided to offer the patient information materials in both paper and digital forms (*i.e.*, website and application). By doing so, and thus tailoring the patient-directed intervention to the infertility population, we hope to increase the effect of this intervention even more.

Aside from the multifaceted and barrier tailored aspects of the strategy, this study has several more strengths.

First, the number of participating clinics is a great strength of this study. One-quarter of all Dutch clinics from all over the country participate in this study, ensuring the representativeness of the Dutch infertility population as well as the professionals who provide fertility care.

Second, the process evaluation provides us with more information on the effectiveness and usefulness of the different interventions used in the strategy and not only of the multifaceted implementation strategy as a whole. We know that the multifaceted aspect of the intervention does not necessarily make the intervention more effective, therefore we need to assess the effectiveness of each individual intervention separately as well [36]. This is of great value for further implementation research and development of implementation strategies. Furthermore, if the multifaceted implementation strategy proves to be effective, it could also be generalized to improve implementation of other guidelines.

Third, the cost evaluation that will take place is very important from a societal aspect. Healthcare is becoming increasingly expensive, and cost reduction is a very important and common topic in most governments and healthcare institutes. This economic evaluation will provide further information on how we can reduce costs in healthcare by following the current and already existing guidelines for best practice and care.

A possible limitation of the study is the chance of contamination of the GPs between the intervention and control group. GPs can refer patients to more than one clinic; this makes it possible that a GP who is allied to an intervention clinic can also refer patients to a control clinic. However, we think that the occurrence of actual contamination will be very small because the participating clinics are very well spread over the country. In case contamination of GPs does occur, we expect the effect on the outcome to be very small or even undetectable because the multifaceted intervention strategy is mostly targeted at the secondary and tertiary care.

In summary, the main contribution of this study is that it seeks to identify the most effective strategy for implementing the guideline on TEM in subfertile couples. Ensuring the appropriate uptake of guideline recommendations by both professionals and patients will improve the care for these patients.

## Abbreviations

TEM: Tailored Expectant Management; ESHRE: European Society of Reproductive Medicine; NICE: National Institute of Health and Clinical Excellence; NVOG: Dutch Society for Obstetrics and Gynecology; MAR: Medically Assisted Reproduction.
